## Abstract

**Background::**

Arthritis is the most common disease in elderly individuals. Many medications for osteoarthritis treatment have the potential for side effects. Using a bioinformatics tool and preclinical studies, ChondroT, 5 herbal complexes, was identified from Ganghwaljetongyeum, which is a18 herbal complex, which has often used to treat osteoarthritis. The goal of this study is to evaluate short-term safety of ChondroT.

**Methods::**

This will be a multicenter, randomized, double-blind, and placebo-controlled trial. There will be a 2-week run-in period before random allocation to 3 groups, ChondroT 1.0 g, 2.0 g, and placebo groups. Total duration of the clinical trial will be 14 weeks including a 4-week washout follow-up. Participants will be followed-up every 4 weeks, and the effect and the safety will be assessed at visit 2, 3, and 4. All participants are asked to maintain the medication schedule in this protocol. The primary outcome will be measured using pain visual analog scale (VAS) after 8 week treatment and secondary outcomes will include pain VAS score after 4 week treatment, SF-36 survey score, patient's global assessment, physical function test, and the change of erythrocyte sedimentation rate, and C-reactive protein. The repeated-measure analysis will be used for the primary efficacy based on full analysis set and per-protocol.

**Discussion::**

This study has restrictive inclusion, exclusion criteria, and a well-controlled intervention, and it will be the first randomized controlled trial to evaluate the efficacy and safety of ChondroT formula in osteoarthritis patients. The trial according to this protocol may provide a new intervention in the treatment of osteoarthritis.

## Introduction

1

Arthritis is the most common inflammatory disease and a major public concern in elderly individuals. The symptoms are characterized by inflammation, pain, and stiffness in the musculoskeletal system and they range from localized self-limiting conditions to systemic autoimmune processes.^[1]^

Various modalities to manage knee joint pain range from conservative management, such as exercise, oral medication including nonsteroidal antiinflammatory agents, and joint injection, to surgical treatment. All medications for osteoarthritis have the potential for side effects^[2–4]^ depending on the type of drugs or individuals involved.

Ganghwaljetongyeum (GHJTY), a mixture of traditional herbs, also has been widely used to improve the symptoms of osteoarthritis in China and Korea. Our previous study showed that GHJTY was effective on rheumatoid arthritis by inhibiting the production of pro-inflammatory mediators and proliferation of synoviocytes.^[5]^ It is a complex herbal decoction composed of 18 plants. In order to improve the efficacy and convenience of pharmaceutical prescription, a previous bioinformatics study^[6]^ identified the 5 medicinal herbs with the greatest potential. These were *Ostericum koreanum* Maximowicz (Osterici Radix, OK), *Lonicera japonica* Thunberg (Lonicerae Folium, LJ), *Clematis mandshurica* Ruprecht (Clematis Radix, CM), *Angelica gigas* Nakai (AngelicaeGigantis Radix, AG), and *Phellodendron amurense* Ruprecht (Phellodendri Cortex, PA). The 5 herbs were extracted with water and named ChondroT. A previous study confirmed that ChondroT had a chondroprotective effect and demonstrated multitarget mechanisms related to inflammation and arthritis which suggest ChondroT's therapeutic potential for the treatment of arthritis.^[7]^

In this study, we designed this study protocol to test if this new drug, ChondroT, is effective on symptoms of osteoarthritis patients by randomized, double-blind, placebo-controlled, multicenter clinical trials.

## Methods and design

2

### Study design

2.1

This will be a multicenter, randomized, double-blind, and placebo-controlled trial. Participants will be recruited through poster or advertisement from arthritis outpatient department in Dongshin University Korean medicine hospitals in Gwangju or Mokpo (DSGOH or DSMPOH). There will be a 2-week run-in period before random allocation to 3 groups, ChondroT 1.0 g, 2.0 g and placebo groups. Total duration of the clinical trial will be 14 weeks including a 4-week washout follow-up. Participants will be followed-up every 4 weeks, and the effect and the safety will be assessed at visit 2, 3, and 4 (Fig. 1).

**Figure 1 F1:**
[figure not shown]
Study design for ChondroT clinical trial. There is a 2-week run-in period before randomization, and follow-up will be 12 weeks including 8-week treatment period with visit once every 4 weeks, and 4-week washout period.

### Ethics approval and consent to participate

2.2

The protocol (version 4.51) of this study has been approved by ethical approval from the institutional review board (IRB) in DSGOH (DSGOH-044, 2017.07.17) and DSMPOH (DSMPOH 17-1, 2017.07.05). For those eligible patients, researchers will give participants the detailed information of this study. Participants or their family should give written informed consent, and then will be enrolled in the study.

Subjects may be required to quit the study in case of serious adverse events or adverse drug reaction, and then they will be reported to institutional review board in both hospitals. In addition, patients may leave this study at any time without any disadvantage or constraint.

Trials are being conducted by supervision of the clinical trial center in both hospitals and monitored by an independent contract research organization (CRO). Especially, a specific clinical research coordinator will coordinate all procedures for participants to improve participants’ adherence to intervention protocols. If there is any change in protocol, it will be approved by IRB again before implementation.

The results will be published on the website of ClinicalTrials.gov in accordance with the CONSORT 2010 Statement and in special journals.

### Selection and inclusion criteria

2.3

Inclusion criteria were as follows: diagnosed as knee osteoarthritis according to the clinical diagnosis of American College of Rheumatology clinical classification criteria;^[8]^ a daily mean pain visual analog scale (VAS) (100 mm Pain VAS) ≥ 40, during the past 1 week (0–100); male or female aged 50 to 80 years.

Exclusion criteria were as follows: receiving immunosuppressant, corticosteroids, cyclosporine, antipsychotics, osteoarthritis medications including painkillers (pas, spray, etc.) or health functional foods to improve joint or cartilage health; having renal functional disorder (more than twice the normal limit of serum creatinine), liver functional disorder (exceeds the normal limit by more than 3 times), connective tissue, multiple sclerosis, inflammatory disease, tumor, trauma, rheumatoid arthritis, autoimmune disease, severe genu valgum or vagus, secondary arthritis, hip disease, or other forms of inflammatory arthritis disease; having a past history such as knee surgery including arthrocentesis drainage or gastrointestinal operations (except for simple appendicitis or hernia) or abuse of drug or alcohol; being treated with traditional medical interventions, steroids, or mucosal supplements injection (hylane, sodium hyaluronate, hyalulonan, etc.) in the knee joint or physical therapy; participating in other clinical trials within 2 months before the screening.

### Intervention and control

2.4

All participants will take 2-week run-in period before randomization, then receive a treatment of 3 groups, ChondroT 1.0 g (2 chondroT tablets + 2 placebo tablets), ChondroT 2.0 g (4 chondroT tablets) or placebo tablet (Table 1) in the following 8-week treatment period. Drugs will be manufactured by Jeongwoo Pharmaceutical Co. and 2 tablets will be orally administered twice daily.

**Table 1 T1:**

Composition of ChondroT tablet.

### Randomization

2.5

Patients will be assigned a patient number, checked whether they meet all the criteria for the enrolment, and then randomized to double blind treatment in a 1:1:1 ratio according to the sequence generated by a computer random program. Both researchers and participants will not know the assignment group because of mimic appearance, smell and taste between ChondroT and placebo treatment drugs. The information on intervention assignment will be stored in the third department of statistics.

### Outcomes

2.6

The primary outcome is pain VAS score, a self-reporting scale for rating severity of pain in osteoarthritis, after 8 week treatment. The secondary outcomes are pain VAS score after 4 week treatment, SF-36 survey score^[9]^ for rating quality of life, patient's global assessment for rating satisfaction of treatment,^[10]^ physical function test for rating functional improvement, and the change of erythrocyte sedimentation rate and C-reactive protein representing inflammation in the body. For safety of drugs, we will conduct the laboratory test, ECG, and vital signs. Safety assessments will be conducted every visit. The assessment of outcomes will be performed by 2 blinded doctors and the average of the 2 doctors’ scores will be determined as final scores.

Participants’ data will be anonymized and coded by a specific program. Double data entry will be entered and monitored by an expert in independent CRO to promote data quality. The final data will be assessed by the principal investigator and the independent statistician. All data during the trial will be stored in archive at clinical trial center in both hospitals.

### Statistical analysis

2.7

Full analysis set (FAS) and per-protocol set (PPS) will be used for the efficacy assessment. According to the principle of intentionality treatment, all patients having the efficacy assessment record at least one time will be brought into the FAS. PPS will include patients who complete the trial and do not violate the protocol.

The primary goal of this study is to test whether ChondroT, a herbal complex, is effective on osteoarthritis patients. Repeated-measures analyses will be used to assess between-group differences in the modeled change in scores from baseline to 12 weeks. Independent variables for fixed effects will be treatment (3 levels: ChondroT 1.0 g, ChondroT 2.0 g and placebo), visit (4 levels: baseline, week 4, week 8, and week 12), interaction between treatment and visit, baseline measures, sex, age, and so on.

For safety analysis, Chi-square test, Fisher exact test, or Wilcoxon rank test will be conducted for assessing the differences of incidence of adverse events (symptoms, signs, diseases, laboratory tests, or abnormal electrocardiogram manifestations) between ChondroT and placebo groups.

All analyses will be performed using the software of Statistics Analysis System, blinded to treatment allocation.

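### The primary outcome is pain VAS after 8 weeks of treatment, but the analysis section states the comparison as change to week 12, four weeks after treatment ends; the model can give the week-8 difference, but the text does not name it

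*Protocol article*

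**What the plan says.** **Primary outcome.** Section 2.6 (Outcomes): "The primary outcome is pain VAS score, a self-reporting scale for rating severity of pain in osteoarthritis, after 8 week treatment". The abstract (Methods) agrees: "The primary outcome will be measured using pain visual analog scale (VAS) after 8 week treatment". Section 2.6 names week-4 pain VAS as a secondary outcome. It does not list week-12 pain VAS at all.

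**Primary analysis.** The abstract identifies the method: "The repeated-measure analysis will be used for the primary efficacy based on full analysis set and per-protocol". Section 2.7 (Statistical analysis) says what that method compares: "Repeated-measures analyses will be used to assess between-group differences in the modeled change in scores from baseline to 12 weeks". The fixed effects listed next include "visit (4 levels: baseline, week 4, week 8, and week 12), interaction between treatment and visit".

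**Timeline.** The Figure 1 legend: "follow-up will be 12 weeks including 8-week treatment period with visit once every 4 weeks, and 4-week washout period". Section 2.1 (Study design): "Total duration of the clinical trial will be 14 weeks including a 4-week washout follow-up".

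**The concern.** The outcome and the comparison meant to test it carry different weeks. Week 8 is the end of treatment; at week 12 every arm has been off study drug for four weeks. The two weeks answer different questions: whether ChondroT reduces pain while it is taken, and whether any benefit lasts after it is stopped.

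The sentence in 2.7 can be carried out in several ways, and only one of them tests the declared outcome. If the analyst reports a week-12 contrast, an average treatment effect over the visits, or an overall test of the interaction, washout data enter the primary efficacy test. If the effect fades after treatment stops, a week-12 contrast could miss a drug that works at week 8. Whatever happens to power, the result would no longer be a test of the outcome declared in 2.6.

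**Working it through.** **1. Where week 12 falls.** From randomization: 8 weeks of treatment + 4 weeks of washout = week 12. With the 2-week run-in: 2 + 8 + 4 = 14 weeks, which matches the total duration in section 2.1. So week 12 is four weeks off treatment.

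**2. The statements side by side.**

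| Place | Role | Time point |
|---|---|---|
| Abstract; 2.6 | Primary outcome, pain VAS | Week 8 |
| 2.6 | Secondary outcome, pain VAS | Week 4 |
| 2.7 | Between-group comparison | Baseline to week 12 |
| 2.7 | Visit levels in the model | Baseline, weeks 4, 8, 12 |

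The only end point in time attached to the comparison is week 12. No sentence in the article reconciles it with week 8.

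**3. Can the model answer the week-8 question?** Yes. With visit as a factor and a treatment-by-visit interaction, the difference between each dose and placebo at week 8 is a linear contrast of the fitted terms. The model needs no change.

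**4. Reproducing the plan's own figure.** Section 2.8 gives 72 patients, 24 per group, about 20% dropout and about 57 completers. 72 × (1 − 0.20) = 57.6, which agrees; 57 / 3 = 19 per arm. The 80% power cannot be reproduced, because no effect size or SD is given.

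**5. Illustration: a pure week-12 contrast.** Inputs from 2.8: two-sided 0.05 and 19 completers per arm. Assumed: a week-8 effect just large enough for 80% power, equal SDs at each visit, and a share f of the effect left at week 12. Two-sample t test with 36 degrees of freedom, critical value 2.028, noncentrality = f × d × √(19/2). Setting power to 80% at f = 1 gives noncentrality 2.879, so d = 2.879 / √9.5 = 0.934 SD. (The normal approximation gives (1.960 + 0.842) × √(2/19) = 0.909.)

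| Share persisting at week 12 | Effect (SD) | Power |
|---|---|---|
| 100% | 0.934 | 80% |
| 75% | 0.701 | 56% |
| 50% | 0.467 | 29% |
| 25% | 0.234 | 11% |
| 0% | 0 | 5% (the type I error rate) |

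**6. Illustration: an average over weeks 4, 8 and 12.** Further assumptions: a common between-visit correlation ρ and a share e of the week-8 effect already present at week 4. Mean effect = d × (e + 1 + f) / 3; SD of the average = √((1 + 2ρ) / 3), which is 0.816 for ρ = 0.5 and 0.894 for ρ = 0.7. Example with ρ = 0.5, e = 1, f = 0.5: 0.934 × 2.5 / 3 = 0.778; 0.778 / 0.816 = 0.953 SD; power 82%.

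| ρ | Week-4 share e | f = 100% | f = 50% | f = 0% |
|---|---|---|---|---|
| 0.5 | 100% | 93% | 82% | 63% |
| 0.5 | 50% | 82% | 63% | 40% |
| 0.7 | 100% | 88% | 74% | 55% |
| 0.7 | 50% | 74% | 55% | 35% |

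Against 80% for the week-8 contrast, the average runs from 35% to 93% over these assumptions. Averaging reduces variance, so it can gain as well as lose.

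**The case against.** The strongest reply is that 12 weeks describes the span of data in the model and not the tested time point. This is a fair reading. The sentence refers to scores in general, most secondary outcomes carry no week of their own, and a model aimed only at week 12 would not need four visit levels and an interaction. If the team then takes the week-8 contrast, there is no mismatch and no loss of power.

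What stands of this: a reader might infer that the trial has settled on a week-12 test and that its analysis cannot answer the primary question. The article does not support that. It nowhere calls week 12 the primary contrast, and its model can estimate the week-8 difference. What does not follow is that the wording is harmless. Even on the span reading, an average effect or an overall interaction test would still include washout data and would still not be the week-8 comparison.

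A second reply is that contrasts are commonly left to the full protocol or the analysis plan, neither of which is shown. That would excuse silence. Here the article gives a week, and it differs from the week of its own primary outcome.

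A reader might also infer that the two weeks leave the team free to pick the better result. That goes too far. Section 2.6 and the abstract consistently fix week 8, week-12 pain is in neither outcome list, and 2.7 says that analyses are done blind to allocation. A switch to week 12 would be a visible departure from the declared outcome.

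**Conclusion.** The article contains a stated conflict: a week-8 primary outcome and a between-group comparison worded as change to week 12, which is off treatment and is not a listed pain VAS outcome. The fault lies in the comparison named, not in the model.

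The size of the consequence is unknown. It depends on which reading is carried out and on an effect size, an SD and a persistence that the article does not give. With the week-8 contrast, nothing is lost. With a pure week-12 contrast, power falls from 80% to 56%, 29% or 5% if 75%, 50% or 0% of the effect persists. With an average over visits, power may be lower or higher than 80%. These figures are illustrations, and a loss of power is possible but not certain. The mismatch with the declared outcome under the last two readings does not depend on any of these assumptions.

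**What to change.** Rewrite the comparison sentence in section 2.7 along these lines: the primary contrast is the model-based difference in pain VAS at week 8 between each ChondroT dose and placebo, taken from the treatment-by-visit term of the repeated-measures model. Keep week 4 as the secondary outcome already stated. Report week 12 separately as a secondary off-treatment contrast that plays no part in the primary conclusion.

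The cost is one sentence in the protocol, repeated in the analysis plan, with the ethics approval that section 2.2 requires for any protocol change. The model, the visits, the data and the 72 patients stay as they are. The change should be made before unblinding.

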### Sample size

2.8

Considering the phase of this study (2a) to evaluate short-term safety of a drug, we have not calculated the sample size based on the previous studies. The sample size is 72 in total and 24 for each group. Assuming a dropout of about 20% and sufficient statistical power of 80% at a significant level of 0.05 in 2 tailed test, about 57 patients may be expected to complete the trials finally.

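### The only safety analysis the article states is difference testing of adverse event incidence, which at 24 per arm cannot bound the excess risk, although short-term safety is given as the study's purpose

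*Protocol article*

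**What the plan says.** The Abstract (Background) states the aim: "The goal of this study is to evaluate short-term safety of ChondroT". Sample size (2.8) and the Discussion also describe this phase 2a trial as an evaluation of short-term safety, and 2.8 gives that as the reason for not deriving the sample size from previous studies. Statistical analysis (2.7), by contrast, names efficacy as the primary goal.

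For safety, 2.7 says: "Chi-square test, Fisher exact test, or Wilcoxon rank test will be conducted for assessing the differences of incidence of adverse events". The comparison is "between ChondroT and placebo groups". It is not stated whether each dose is compared with placebo separately or the two doses are pooled.

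On size, 2.8 says: "The sample size is 72 in total and 24 for each group". Patients are "randomized to double blind treatment in a 1:1:1 ratio" (Randomization, 2.5). Section 2.8 also mentions "sufficient statistical power of 80% at a significant level of 0.05 in 2 tailed test", without naming an endpoint, an effect size or an event rate.

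Outcomes (2.6) plans laboratory tests, ECG and vital signs, with safety assessed at every visit. That describes what is collected, not how it is summarised.

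**The concern.** A test of no difference can flag a large harm. It cannot show that a harm is absent or small. If evaluating safety is the purpose, the useful quantity is the excess risk over placebo that the data leave open, and a p-value does not give it.

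At this sample size, a non-significant comparison is the likely result even if the drug raises event rates by a moderate and clinically relevant amount. If the report contained only the stated analysis, a reader would see no significant difference and could not tell whether the data exclude a large excess or are merely too few to detect it. The 80% power figure in 2.8 might be taken as reassurance. It offers none for safety, because it is attached to no endpoint or effect.

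**Working it through.** **Inputs from the article:** 72 patients, 24 per arm, 1:1:1 allocation, dropout of about 20%, two-sided 0.05. The significance level is stated for the sample size; I assume it also applies to the safety tests.

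**Assumed:** adverse event rates, since the article gives none. I use placebo rates of 5% and 10% with a range of increases.

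**Step 1: the plan's own figures.** 72 × (1 − 0.20) = 57.6, which agrees with the stated figure of about 57 completers. Per arm, 19 / 0.80 = 23.75, which rounds up to 24. The 80% power cannot be reproduced for any endpoint. By the normal approximation it implies a standardised difference of (1.960 + 0.842) × √(2/24) = 0.81 on a continuous outcome, which says nothing about event incidence.

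**Step 2: power of the stated tests.** For every pair of counts (x on placebo, y on drug), take the binomial probability of that pair under the assumed rates and add it up over all pairs with p ≤ 0.05:

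Power = Σ Bin(x; n₀, p₀) × Bin(y; n₁, p₁) × 1[p(x, y) ≤ 0.05]

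| Placebo vs drug (assumed) | Fisher, 24 v 24 | Chi-square, 24 v 24 | Fisher, 48 pooled v 24 | Chi-square, 48 pooled v 24 |
|---|---|---|---|---|
| 5% vs 15% | 10.6% | 20.2% | 14.5% | 21.1% |
| 5% vs 20% | 23.7% | 36.5% | 32.4% | 40.7% |
| 10% vs 30% | 31.4% | 43.1% | 42.8% | 50.3% |
| 10% vs 40% | 60.2% | 71.2% | 76.9% | 81.7% |

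For the first three rows, Fisher's test misses the increase in 69–89% of trials at 24 v 24 (1 − 0.314 to 1 − 0.106) and in 57–86% with pooling (1 − 0.428 to 1 − 0.145). At 24 v 24, Fisher reaches 80% power only at about 5% vs 39% or 10% vs 49%.

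**Step 3: what a non-significant result looks like.** With no events on placebo, Fisher needs at least 5/24 (21%) on drug:
- 4/24 vs 0/24: p = 2 × C(24,4)/C(48,4) = 2 × 10,626/194,580 = 0.109
- 5/24 vs 0/24: p = 2 × C(24,5)/C(48,5) = 2 × 42,504/1,712,304 = 0.0496

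**Step 4: what an interval adds.**
- 3/24 vs 1/24: Fisher p = 0.61. The difference is 8.3 points, with a Newcombe 95% interval of −9.7 to +27.2 points.
- 5/24 vs 2/24: Fisher p = 0.42. The difference is 12.5 points, with an interval of −8.5 to +33.0 points.
- No events at all: the exact two-sided 95% upper limit is 1 − 0.025^(1/n). This is 14.2% for n = 24 and 7.4% for n = 48.

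In both two-arm examples the p-value looks unremarkable, while the interval shows that an excess of more than 25 points has not been excluded.

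**The case against.** The strongest objection is that the article never says what the concern fears. A reader might infer that a non-significant test will be reported as proof of safety. Section 2.7 states no such rule, no success criterion and no wording for a safety conclusion, so that inference is not supported. This stands.

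A reader might also infer that safety will be judged by these tests alone. The article condenses a fuller protocol, and counts, listings or intervals may be specified there or in an analysis plan. All that can be said is that testing is the only safety analysis stated here. This stands too.

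Third, it would be too strong to say that the trial would miss most real harms. The result depends on assumed rates. An increase from 10% to 40% is found more often than not, and Fisher is conservative: with pooled doses, chi-square finds 10% vs 30% about half the time. The claim holds for moderate increases only.

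Fourth, low power for adverse events is usual at this phase, 2.7 calls efficacy the primary goal, and the Discussion concedes the small sample. All true. But low power is the reason to estimate rather than test, and no larger trial is being asked for. Naming efficacy as primary in one place does not withdraw the safety purpose given in three others. The Discussion's caveat is general and is not linked to the safety tests.

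Finally, a reader might fault the listing of three tests without a selection rule. That is common shorthand, and the rule belongs in the analysis plan, so no point is made of it.

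**Conclusion.** The point holds as a mismatch between stated purpose and stated method. The article gives short-term safety as the study's purpose, and the analysis it states for safety cannot bound the excess risk. For the assumed rates of 5% vs 15%, 5% vs 20% and 10% vs 30%, Fisher power is about 11–31% for a single dose against placebo and 15–43% with both doses pooled. It rises to 60% and 77% for 10% vs 40%. A non-significant result therefore could not support a statement of safety.

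This rests on the assumed event rates, on two-sided 0.05 applying to the safety tests, and on all 24 patients per arm being analysed. With only 19 per arm, power would be lower (22% by Fisher for 10% vs 30%). It does not show that the sponsor intends to misread the tests, or that the full protocol lacks estimates. It is a worthwhile and inexpensive improvement rather than an error that invalidates the trial.

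**What to change.** In 2.7, make estimation the basis of the safety assessment:

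- For adverse events overall and by category, report the number and proportion of patients with at least one event in each arm, with exact (Clopper-Pearson) 95% confidence intervals.
- Report the risk difference of each dose against placebo with a Newcombe or Miettinen-Nurminen 95% confidence interval.
- State that p>0.05 will not be taken as evidence of safety. The tests may stay as supportive.

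This takes a few sentences and some table columns, and needs no extra patients or data. The price is that the intervals will be wide and the safety conclusion more modest: even with no events in 24 patients, a true rate of up to about 14% would remain compatible with the data.
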